#### Exclusion criteria

2.2.3

Individuals who meet any of the following criteria cannot participate in the study.

Individuals for whom LivaloZet^®^ Tablets is contraindicated as specified in the label’s Precautions for Use.Individuals who were treated with other investigational products (IP) or investigational devices within 4 weeks prior to participation in the present study or who are expected to have such treatment during the present study.Patients with conditions that may preclude safe use of pitavastatin or ezetimibe, including: active liver disease or persistent elevations of serum transaminases (AST or ALT >3× ULN); severe renal impairment (eGFR <30 mL/min/1.73 m²) or end-stage renal disease on dialysis; uncontrolled hypothyroidism (TSH >10 mIU/L); active myopathy or unexplained CK elevation >5× ULN at baseline; rhabdomyolysis history; pregnancy, lactation, or planned pregnancy during the study period; and severe systemic illness expected to limit participation or survival during the 48-week observation period. Conditions covered by the LivaloZet^®^ product label contraindications are excluded under criterion 1) above.Individuals who are considered to have difficulty participating in the study for other reasons based on the judgment of the investigator.

### Cardiovascular risk classification

2.3

Cardiovascular risk classification (**Table 2**) is assigned by the treating investigator at Visit 1 (baseline), based on the patient’s clinical history, comorbidities, and available risk-factor data, in accordance with the 2022 KSoLA guidelines (9). If risk-factor data are incomplete for any participant, the investigator will assign the most conservative (higher-risk) category supported by available evidence, and the participant will be flagged for sensitivity analysis. Risk classification will not be re-assigned during follow-up; the baseline category determines target LDL-C used for goal-attainment analyses.

### Efficacy endpoints

2.4

#### Primary endpoint

2.4.1

Percent change from baseline in LDL-C level at Week 24 (calculated, see Section 2.6.4 for LDL-C measurement method).

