^4)^Medical history (including surgical/procedure history) within 12 weeks prior to Visit 1 will be collected. For medical history relevant to the inclusion and exclusion criteria, information throughout lifetime will be collected, unless otherwise specified.

^5^Medication information on lipid regulators, antidiabetics, and other drugs will be collected. Drugs administered within 4 weeks prior to Visit 1 will be collected as prior medication. If there is a history of treatment with lipid regulators within the predefined duration of information collection for prior medication, medication information on lipid regulators within 8 weeks prior to Visit 1 will be collected. In addition, if results of prior serum lipid or blood glucose and glucose metabolism parameter tests are used as baseline (Visit 1) results, information on lipid regulators will be collected in the same manner as described above based on the time point of the tests. Drugs administered from after the first study drug dosing to the end of observation will be collected as concomitant medication.

^6)^Height, weight and waist circumference will be measured, and body mass index (BMI) will be calculated. Height will be measured at Visit 1 only.

^7)^LDL-C, TC, TG, HDL-C, and non-HDL-C will be tested. LDL-C may be measured either directly (by homogeneous direct assay) or calculated using the Friedewald formula; when TG ≥400 mg/dL, direct LDL-C measurement is required (Section 2.7). If test results obtained within 4 weeks prior to Visit 1 are available and the participant had no treatment with lipid regulators within 4 weeks prior to the test or was treated with lipid regulators using the same dosage and administration for at least 8 weeks, the test results may be used as baseline (Visit 1) results. Before testing, a blood sample is to be collected after at least 12 hours of fasting, if possible; If it is difficult for the participant to remain fasted for 12 hours, at least 9 hours of fasting should be maintained.

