#### Handling of missing data

2.6.4

In the event of missing data, missing values for efficacy endpoints are imputed using the last observation carried forward (LOCF) method. However, baseline values are not carried forward to replace post-baseline values. Safety analyses are conducted using observed cases (OC) without imputation of missing data. LOCF was selected as the primary approach for efficacy endpoints because it is a widely accepted, conservative, and easily interpretable method in regulatory and observational research, and because in a single-arm descriptive study without between-group comparison the bias introduced by LOCF is generally toward attenuation of within-participant change rather than spurious between-group differences. We acknowledge, however, that LOCF assumes that the last observed value is representative of the subsequent (missing) value, which may not hold for participants who discontinue treatment due to lack of efficacy or adverse events; the multiple sensitivity analyses described below (observed cases, multiple imputation, MMRM) are therefore essential to evaluate the robustness of the primary findings in this 48-week observational setting. To address the potential bias introduced by LOCF, two sensitivity analyses will be performed: (i) observed-cases analysis without imputation; and (ii) multiple imputation under the missing-at-random assumption (m=20 imputations, predictive mean matching). Mixed-effects models for repeated measures (MMRM) including all available longitudinal observations will be conducted as an additional sensitivity analysis, with no imputation required. The robustness of the primary conclusion will be assessed by comparing point estimates and confidence intervals across these analytical approaches.

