### Laboratory measurements and quality control

2.7

Lipid panel (LDL-C, TC, TG, HDL-C, non-HDL-C) and safety laboratory tests (AST, ALT, CK) are performed at each participating center’s local laboratory using standard clinical assays. LDL-C may be measured either directly (by homogeneous direct assay) or calculated using the Friedewald formula. When TG ≥400 mg/dL, the Friedewald formula is invalid and direct LDL-C measurement is required; in such cases, non-HDL-C will be used as a supplementary measure. The LDL-C measurement method (direct vs calculated) will be recorded for every measurement and analyzed as a covariate. To address inter-laboratory variability, all participating laboratories must be certified under the Korean Laboratory Accreditation Scheme or equivalent national/international standards, and external quality assurance (EQA) results will be reviewed annually. Site-level training will be provided prior to study initiation, including standardized fasting requirements (≥12 hours preferred, ≥9 hours minimum for lipid and glucose testing), standardized variable definitions, and standardized data entry procedures. Electronic case report forms include built-in range and consistency checks. Independent monitoring visits will be conducted at high-enrolling centers, with remote source data verification at all sites. Discrepancies will be addressed through formal data queries.

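### Section 2.4.1 calls the primary LDL-C calculated and cites the wrong section, while Section 2.7 lets the method differ between baseline and Week 24; a simple method covariate leaves the overall mean unchanged

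*Protocol article*

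**What the plan says.** Section 2.4.1 gives the primary endpoint as percent change in LDL-C at Week 24 and adds in parentheses "calculated, see Section 2.6.4 for LDL-C measurement method".

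Section 2.6.4 is the missing-data section. Its subject is that "missing values for efficacy endpoints are imputed using the last observation carried forward (LOCF) method", with the sensitivity analyses that follow from it. It contains nothing on how LDL-C is measured.

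The method rule is in Section 2.7: "LDL-C may be measured either directly (by homogeneous direct assay) or calculated using the Friedewald formula". When TG reaches 400 mg/dL, "the Friedewald formula is invalid and direct LDL-C measurement is required". Footnote 7 of Table 1 repeats both rules and points correctly to Section 2.7.

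On analysis, Section 2.7 says that the method "will be recorded for every measurement and analyzed as a covariate". It does not say whether the covariate is the baseline method, the Week 24 method or the pair.

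Footnote 7 also lets an earlier test serve as baseline: "If test results obtained within 4 weeks prior to Visit 1 are available", subject to conditions on lipid-regulator treatment. None of these conditions concerns the method.

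**The concern.** The sentence that defines the primary variable has two faults. Its reference leads to a section that does not answer the question. Its word for LDL-C, if it describes the method, contradicts the two-method rule in Section 2.7 and Table 1.

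The gap behind the wording matters more. Below 400 mg/dL of TG the method is free at each visit, and at or above it direct measurement is forced. A participant can therefore have a direct value at baseline and a calculated one at Week 24, or the reverse. Any systematic difference between the methods then enters that participant's percent change. TG of 200 mg/dL or more is a qualifying criterion for dyslipidemia (Section 2.2.1), and TG change is itself a secondary endpoint. Some switching may therefore follow treatment response.

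Precision is the first reason given for the sample size in Section 2.5. A method difference in the mean would not shrink as enrollment grows.

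**Working it through.** **The plan's own precision.** Section 2.5 gives 8,000 analysed participants, SD 22% and a two-sided 95% interval. Half-width = 1.96 × 22 / √8000 = 0.48 points, so the stated ±0.5% reproduces.

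**Assumed inputs.** The documents give no method offset, no share of switchers and no expected mean baseline LDL-C. I assume that direct reads d = 5 to 10 mg/dL above calculated, baseline L0 = 100 to 160 mg/dL, and net direct-to-calculated switching s = 2% to 20%. If direct read lower, the sign would reverse.

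**Shift with direct as the reference.** Shift per switcher = 100 × d / L0; shift in the mean = that × s.
- L0 = 130: 5/130 = 3.8 points and 10/130 = 7.7 points per switcher.
- Smallest corner: 100 × 5/160 × 0.02 = 0.06 points.
- Largest corner: 100 × 10/100 × 0.20 = 2.0 points.
- Share at which the shift equals the half-width, at L0 = 130: 0.482/3.85 = 12.5% (d = 5) or 0.482/7.69 = 6.3% (d = 10).

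**Shift with calculated as the reference.** The offset now sits in the baseline value. For an illustrative true reduction of 50% (the Discussion cites 52-53% from a phase III trial), the shift per switcher is 100 × 0.5d / (L0 + d).
- L0 = 130: 2.5/135 = 1.9 points and 5/140 = 3.6 points per switcher, about half the values above.
- Corners: 100 × 2.5/165 × 0.02 = 0.03 points and 100 × 5/110 × 0.20 = 0.91 points.

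**Does the covariate help?** In a simulation, direct was the truth, d = 5, 12% switched direct-to-calculated and 3% calculated-to-direct, and the true mean was -49.99%.

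| Analysis | Estimate |
|---|---|
| Unadjusted mean | -51.24% |
| Adjusted, at covariate means: baseline method, Week 24 method, both, or pair | -51.24% in all four |
| Baseline method only, at direct / at calculated | -50.84% / -51.78% |
| Week 24 method only, at direct / at calculated | -49.87% / -52.50% |
| Both visits' methods, at direct-direct | -49.99% |

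The second row is an identity: least squares evaluated at the covariate means returns the raw mean. The bias goes only when the model knows the method at both visits and the estimate is taken at a same-method pair.

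The simulation shows how the covariate behaves, not how large the switching effect is. Its 1.25-point gap splits by group share × group bias:
- calculated at both visits: 0.401 × (-2.09) = -0.84;
- direct-to-calculated: 0.120 × (-4.00) = -0.48;
- calculated-to-direct: 0.030 × 2.09 = +0.06.

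Switching accounts for -0.42. The remainder arises because a constant offset changes the denominator even when the method stays the same.

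**The case against.** **The textual error is editorial.** A reader can find the rule through Table 1, and the disputed word might describe the percent change rather than the method. That is possible, but the word stands next to a mention of measurement method, and Section 2.7 contrasts direct with calculated. On either reading the sentence needs correcting.

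**Covariate coding can be left to the analysis plan.** This stands in part. A reader might infer that no covariate approach could work. The documents do not support that: the coding is open, a method-pair term could remove a constant offset, and so could a visit-level model with time-varying method. Section 2.6.4 already lists an MMRM as a sensitivity analysis, though it does not mention method.

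**The size is unsupported.** This stands. A reader might infer a demonstrated artefact that is a multiple of the stated precision. No document gives the share crossing 400 mg/dL, and eligibility does not imply a large one, because TG is only one of several alternative criteria. A participant whose laboratory always uses the direct assay never switches, and opposite switches partly cancel.

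**Target attainment.** A reader might extend the point to the secondary attainment rates. Attainment uses the value at one visit, so switching within a participant does not affect it. Differences between methods at a single visit are a separate matter, which the plan treats in general terms through accreditation, EQA and a stated limitation on inter-laboratory variability.

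**Dropping mixed pairs would select on TG response.** This stands, so their exclusion belongs in a sensitivity analysis only.

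**Conclusion.** The point holds as a fault in how the primary variable is defined. The cross-reference is wrong, the label conflicts with Section 2.7 and Table 1 on its natural reading, and no rule keeps the method constant within a participant. The covariate, entered simply, leaves the single-arm mean where it was.

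Whether this matters numerically cannot be settled from the documents. Under the assumed ranges the mean moves by 0.06 to 2.0 points with direct as the reference, or 0.03 to 0.91 with calculated as the reference and a 50% reduction. Against 0.48, that runs from negligible to larger than the claimed precision. All of this rests on assumed values for offset, baseline and net one-directional switching, so it shows what is possible and does not demonstrate a bias. The change is worth making because the required data already permit a same-method variable at almost no cost.

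**What to change.** 1. In Section 2.4.1, point to Section 2.7, and either remove the word for the method or make it true.
2. For the primary change, use one method at both visits. Serum lipids, including TC, HDL-C and TG, are required at all three visits in Table 1. Derive LDL-C by one formula whenever TG is below 400 mg/dL at both baseline and Week 24. Otherwise use direct values at both visits where available.
3. Keep the remaining mixed-method pairs in the FAS analysis, flagged.
4. Add a sensitivity analysis restricted to same-method pairs, and show the non-HDL-C change, already a secondary endpoint, alongside.
5. If method stays as a covariate, state that it is the baseline/Week 24 pair, or time-varying in a visit-level model, and at which pair the estimate is taken.

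Cost: one derived variable, some wording and no new tests. The downside is greater reliance on the Friedewald formula, including at low LDL-C, so an analysis using the reported direct values should be shown as a further sensitivity analysis.

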#### Secondary endpoints

2.4.2

Percent change from baseline in LDL-C level at Week 48.Absolute change from baseline in LDL-C level at Week 24 and Week 48.Percent change and absolute change from baseline in lipid parameters at Week 24 and Week 48: Total cholesterol (TC), triglyceride (TG), HDL-C, non-HDL-C. Apolipoprotein B (Apo B) is not a required measurement; it will be collected and analyzed descriptively only when available from routine clinical practice.Achievement rate (%) for target LDL-C level at Week 24 and Week 48: Very high risk group <55 mg/dL, high risk group <70 mg/dL, diabetes group <100 mg/dL, moderate risk group <130 mg/dL, and low risk group <160 mg/dL according to the classification of cardiovascular disease risk groups.Medication adherence (proportion of days covered, PDC), persistence (time from initiation to discontinuation), dose modifications, and treatment switching during the 48-week observation period.

#### Safety endpoints

2.4.3

Adverse events (AEs), classified by severity (mild, moderate, severe), causality to study medication (related, possibly related, unrelated), and seriousness (serious vs. non-serious) according to ICH-E2A criteria.Laboratory tests (blood chemistry), including systematic monitoring of AST, ALT, and creatine kinase (CK) at every visit for assessment of statin-related hepatotoxicity and myopathy. Pre-specified thresholds for safety signals are: AST or ALT >3× upper limit of normal (ULN); CK >5× ULN with muscle symptoms, or >10× ULN regardless of symptoms.Vital signs.Pre-specified adverse events of special interest: hepatotoxicity, myopathy, rhabdomyolysis, new-onset diabetes mellitus, and discontinuation due to AEs.

#### Exploratory endpoints

2.4.4

Absolute change from baseline in blood glucose and glucose metabolism parameters at Week 24 and Week 48: Hemoglobin A1c (HbA1c), homeostasis model assessment of insulin resistance (HOMA-IR), homeostasis model assessment of β-cell function (HOMA-β).Percent change and absolute change from baseline in high sensitivity C-reactive protein (hs-CRP) at Week 24 and Week 48.

Exploratory laboratory parameters (HbA1c, HOMA-IR, HOMA-β, hs-CRP) are collected when available from routine clinical practice and are therefore subject to non-random missingness. To mitigate this limitation, baseline characteristics will be compared between participants with and without available measurements, and inverse-probability-of-availability weighting will be considered as a sensitivity analysis when interpreting these endpoints.

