^8)^If test results for HbA1c, HOMA-IR, and HOMA-β are available, the information will be collected. If it is not feasible to collect HbA1c test results within the visit window in patients with pre-diabetes or diabetes, HbA1c testing will be performed. If test results obtained within 4 weeks prior to Visit 1 are available and the participant had no treatment with lipid regulators within 4 weeks prior to the test or was treated with lipid regulators using the same dosage and administration for at least 8 weeks, the test results may be used as baseline (Visit 1) results. Before testing, at least 8 hours of fasting should be maintained.

^9)^If test results for hs-CRP are available, the information will be collected. If test results obtained within 4 weeks prior to Visit 1 are available and the participant had no treatment with lipid regulators within 4 weeks prior to the test or was treated with lipid regulators using the same dosage and administration for at least 8 weeks, the test results may be used as baseline (Visit 1) results.

^10)^Aspartate aminotransferase (AST), alanine aminotransferase (ALT), and creatine kinase (CK) are collected systematically at every visit to monitor statin-related hepatotoxicity and myopathy. If test results obtained within 4 weeks prior to Visit 1 are available, they may be used as baseline (Visit 1) results. Pre-specified safety thresholds for action: AST or ALT >3× upper limit of normal (ULN); CK >5× ULN with muscle symptoms, or >10× ULN regardless of symptoms (Section 2.4.3).

^11)^Apolipoprotein B (ApoB) is not a required measurement; it will be collected and analyzed descriptively only when available from routine clinical practice (Section 2.4.2).

^12)^Medication adherence (proportion of days covered, PDC), persistence (time from initiation to discontinuation), dose modifications, and treatment switching will be collected at follow-up visits (Section 2.4.2).

^13)^All clinically significant medical conditions or abnormalities occurring from the first study drug dosing to the EOS visit will be collected as AEs. Any unresolved AEs at the time of the participant’s EOS visit will be followed until resolution, stabilization, or for a minimum of 4 weeks after the EOS visit, whichever is later, with extended follow-up at the investigator’s discretion for serious or clinically significant events (Section 2.1).

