#### Inclusion criteria

2.2.2

To be eligible for this study, participants must meet all of the following criteria.

Age ≥19 years old at the time of written informed consent.Participants diagnosed with dyslipidemia and metabolic syndrome as defined in Section 2.2.1.Participants who had no treatment history with lipid regulators within 4 weeks prior to Visit 1 or who had insufficient therapeutic effects from ≥8 weeks of treatment with lipid regulators using the same dosage and administration (these two subgroups—treatment-naïve and inadequate-response—will be pre-specified and analyzed separately as a key subgroup analysis, as they may exhibit differential LDL-C response).Participants who meet the following LDL-C levels according to the classification of cardiovascular disease risk groups (9) (**Table 2**) at Visit 1 or who are planned to be treated with LivaloZet^®^ Tablets based on the judgment of the investigator.Participants who voluntarily sign the informed consent form for study participation.

**Table 2 T2:** Classification of cardiovascular risk groups and target LDL-C level.

Risk group	Criteria for classification	LDL-C (mg/dL)
Very high risk group	Coronary artery disease	≥ 55
High risk group	Atherosclerotic ischemic stroke, transient ischemic attack, carotid artery disease, peripheral arterial disease, abdominal aortic aneurysm, diabetes mellitus (duration of disease ≥10 years; or concurrent major cardiovascular disease risk factors† or target organ damage‡)	≥ 70
Diabetes group	Diabetes mellitus (duration of disease <10 years, no major cardiovascular disease risk factors†)	≥ 100
Moderate risk group	≥2 major cardiovascular disease risk factors†	≥ 130
Low risk group	≤1 major cardiovascular disease risk factor†	≥ 160

† Major cardiovascular disease risk factors (1): Age: ≥ 45 years old in men, ≥ 55 years old in women; (2) Family history of early onset coronary artery disease: Parents or siblings who had an onset of coronary artery disease at the age of <55 years in men and <65 years in women; (3) Hypertension: Systolic blood pressure (SBP) ≥ 140 mmHg or diastolic blood pressure (DBP) ≥ 90 mmHg or treatment with antihypertensives; (4) Current smoking; (5) High density lipoprotein-cholesterol (HDL-C) < 40 mg/dL (If HDL-C ≥ 60 mg/dL, 1 will be subtracted from the number of major risk factors).

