#### Subgroup analyses

2.6.3

Pre-specified subgroup analyses will be performed for the primary endpoint by: (1) cardiovascular risk category; (2) prior lipid-lowering treatment history (treatment-naïve vs inadequate response); (3) dose (2/10 mg vs 4/10 mg); (4) age (<65 vs ≥65 years); (5) sex; (6) presence of diabetes mellitus; and (7) baseline LDL-C (<130 vs ≥130 mg/dL). Subgroup analyses are descriptive; no formal interaction testing is planned.

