Statins remain the cornerstone of pharmacological lipid management, and their combination with ezetimibe has been well established as an effective and safe approach for patients who require potent LDL-C reduction or who cannot tolerate high-dose statin monotherapy (9, 11, 12). Prior randomized controlled trials provide the biological and clinical rationale for the present study. The landmark IMPROVE-IT trial demonstrated that adding ezetimibe to statin therapy significantly reduced major cardiovascular events compared with statin monotherapy, providing compelling evidence that non-statin LDL-C lowering translates into clinical benefit (24). Furthermore, the RACING trial confirmed that moderate-intensity statin combined with ezetimibe achieves non-inferior LDL-C reduction with fewer adverse events compared with high-intensity statin monotherapy (25). However, because the present study is a single-arm observational design without a comparator, it cannot replicate the comparative inferences of these randomized trials. Rather, the present study complements such trials by providing descriptive real-world data on routine clinical use. Among statins, pitavastatin is distinguished by its relatively neutral effect on glucose metabolism, compared with several other statins (10, 21–23). Meta-analyses and randomized trials have demonstrated that pitavastatin has a comparatively favorable profile with respect to fasting glucose, HbA1c, and insulin sensitivity, making it a particularly attractive option for patients with metabolic syndrome who frequently have impaired glucose metabolism or established type 2 diabetes (21–23). A recent phase III randomized trial in Korean patients confirmed that pitavastatin/ezetimibe combination therapy achieved superior LDL-C reduction of approximately 52-53% from baseline compared with pitavastatin monotherapy (37-45%), with a comparable safety profile (26). The fixed-dose combination of pitavastatin and ezetimibe in LivaloZet^®^ Tablets is thus a rationally designed therapeutic option that addresses both the lipid-lowering needs and the metabolic concerns of this patient population.

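### The split by prior lipid-lowering treatment is fixed for LDL-C only, so the HbA1c and HOMA changes pool patients starting from no treatment with patients switching from another statin

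*Protocol article*

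**What the plan says.** **Who is enrolled.** Criterion 3 in section 2.2.2 of the protocol article takes "Participants who had no treatment history with lipid regulators within 4 weeks prior to Visit 1 or who had insufficient therapeutic effects from ≥8 weeks" of an unchanged regimen. It says that these two groups will be "analyzed separately as a key subgroup analysis, as they may exhibit differential LDL-C response".

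**Where the split applies.** Section 2.6.3 reads "Pre-specified subgroup analyses will be performed for the primary endpoint by: (1) cardiovascular risk category; (2) prior lipid-lowering treatment history", followed by five further factors. No other endpoint is named there.

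**Glucose endpoints.** Section 2.4.4 lists "Absolute change from baseline in blood glucose and glucose metabolism parameters at Week 24 and Week 48", namely HbA1c, HOMA-IR and HOMA-β, without stratification. New-onset diabetes is an adverse event of special interest in section 2.4.3, also without stratification.

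**Baseline.** Table 1 footnote 8 allows a glucose result from the 4 weeks before Visit 1 to serve as baseline if the participant was untreated or "was treated with lipid regulators using the same dosage and administration for at least 8 weeks, the test results may be used as baseline".

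**Premise and purpose.** The Discussion states: "Among statins, pitavastatin is distinguished by its relatively neutral effect on glucose metabolism, compared with several other statins". It then presents the glucose results as a description of the product's metabolic safety.

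**The concern.** Change from baseline means something different in the two enrolled groups. For a patient off lipid regulators, it compares the product with no current lipid drug. For a patient moved from another statin, the earlier drug's effect on glucose is already in the baseline, so the change compares two statins. If pitavastatin is kinder to glucose than the statin left behind, as the article argues, the second group's HbA1c could fall while the first group's rises.

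An average over both groups depends on the case mix, which the plan does not fix. A pooled change near zero could then be taken as metabolic neutrality although neither group is near zero. The protocol recognises that prior treatment changes the LDL-C response, but it does not carry the same reasoning to the endpoints on which its metabolic-safety description rests.

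**Working it through.** **1. The plan's own figures (section 2.5).** These reproduce and are not in dispute.
- Half-width of the 95% interval for LDL-C, with SD 22% and n = 8,000: 1.96 × 22 / √8,000 = 0.48, against a stated ±0.5%.
- Chance of at least one adverse event at a true rate of 0.04%: 1 − (1 − 0.0004)^8,000 = 0.959, against a stated minimum of 80%.

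**2. Does any other provision separate the groups for glucose?**
- Availability weighting (section 2.4.4) deals with which patients have a test, not with what they took before.
- Propensity adjustment (section 2.6.5) uses prior therapy only as a covariate when dose groups are analysed.
- The Discussion warns that patients with different treatment histories may differ, but the remedy it cites is that same propensity adjustment.

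None of these separates starters from switchers for HbA1c or HOMA.

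**3. What pooling can do.** The document gives no effect sizes and no group shares, so all three inputs are assumptions:
- e = HbA1c change caused by the product relative to no statin: +0.05 points
- d = HbA1c effect of the earlier statin, already in the baseline: 0.05 to 0.15 points
- s = share of participants switched from such a statin: 30% to 70%

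Starters change by e and switchers by e − d, so

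pooled change = (1 − s)·e + s·(e − d) = e − s·d

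| s | d | Starters | Switchers | Pooled |
|---|---|---|---|---|
| 0.3 | 0.05 | +0.05 | 0.00 | 0.05 − 0.015 = +0.035 |
| 0.5 | 0.10 | +0.05 | −0.05 | 0.05 − 0.050 = 0.00 |
| 0.7 | 0.15 | +0.05 | −0.10 | 0.05 − 0.105 = −0.055 |

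The same effect in starters can appear as a small rise, as nothing, or as a fall. A second set of assumptions agrees. With +0.10 in starters and −0.10 in switchers, the pooled change is −0.06, 0.00 or +0.06 when starters are 20%, 50% or 80% of the sample.

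**4. Can the strata be estimated?** Assume an HbA1c SD of 0.8, results available in 20% to 80% of 8,000 participants, and a stratum share of 20% to 80%.
- Smallest stratum: n = 8,000 × 0.2 × 0.2 = 320, half-width 1.96 × 0.8 / √320 = 0.088.
- Largest stratum: n = 8,000 × 0.8 × 0.8 = 5,120, half-width 1.96 × 0.8 / √5,120 = 0.022.

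The split is feasible for HbA1c, although the smallest strata could not resolve a change of 0.05.

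**5. Rare adverse events within a stratum.** If starters are an assumed 20% of 8,000, 1 − 0.9996^1,600 = 0.473. At 50%, 1 − 0.9996^4,000 = 0.798. Both are below the 80% stated for the whole study.

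**The case against.** **The split may be planned elsewhere.** Criterion 3 promises separate analysis in general terms, section 2.5 mentions descriptive analyses by treatment history, and tables of exploratory and safety results by subgroup are often left to an analysis plan that is not shown. This has weight. But section 2.6.3 is the operative text and names the primary endpoint, and the reason given in criterion 3 is LDL-C response. As written, the glucose endpoints fall outside the split.

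**The study claims no neutrality and no causation.** True. The abstract and Discussion confine the findings to description and urge caution with the glucose results. That limits the severity. A descriptive average is still hard to read when it mixes two contrasts.

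**The cancellation is hypothetical.** Also true. Criterion 3 speaks of lipid regulators, so earlier treatment could be ezetimibe, a fibrate or pitavastatin itself. For such patients there may be no glucose-raising statin effect to remove, and s counts only those leaving a statin that raised glucose.

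**A tempting extension to adverse events and AST, ALT and CK.** A reader might infer that pooled safety results understate the risk of new starters, because switchers have already tolerated a statin. If switchers had 0.5 to 0.7 times a starter's risk and made up 30% to 70% of the sample, the pooled incidence would lie s·(1 − r) = 9% to 35% below that of starters. The document does not support that ratio or its direction. The Introduction says that the product is also meant for patients in whom adverse effects rule out high-dose statins, so switchers may be more prone to events. Prior drugs need not be statins. The laboratory signals are absolute multiples of the upper limit of normal, not changes from baseline.

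**Conclusion.** The concern holds for the glucose endpoints. The protocol enrols two groups with different baselines, accepts an on-treatment glucose baseline, and fixes the prior-treatment split for LDL-C only. Its own premise about pitavastatin gives reason to expect the two groups' glucose changes to differ.

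Masking is possible, not shown. The range of +0.035 to −0.055 for a true +0.05 rests entirely on assumed effects and shares, and on the assumption that the earlier statin's effect has worn off by the time of measurement. HbA1c and HOMA are exploratory and descriptive, so this is a worthwhile correction rather than a threat to the study's main result. New-onset diabetes, as an adverse event of special interest, adds some weight.

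Two stronger readings are not supported. No direction of bias can be asserted for the pooled adverse-event, AST, ALT or CK results. Nor does the off-treatment stratum give the causal effect of starting the product: it is an uncontrolled before-after change with lifestyle counselling at every visit. That stratum requires only 4 weeks without lipid regulators and so is not strictly statin-naïve. Footnote 5 looks back 8 weeks only if a lipid regulator was used in the last 4, so a statin stopped at week 5 goes unrecorded.

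**What to change.** In section 2.6.3, extend the prior-treatment split to HbA1c, HOMA-IR, HOMA-β and new-onset diabetes, with three strata taken from the medication record in Table 1 footnote 5:
1. off lipid regulators for at least 4 weeks;
2. on a statin at baseline;
3. on a non-statin lipid regulator at baseline.

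Report the strata descriptively beside the pooled result. Label the on-statin stratum as change after a switch. State that the off-treatment stratum is not strictly statin-naïve and carries no causal reading. Do not base a statement of metabolic neutrality on the pooled change alone.

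Adverse events and AST, ALT and CK threshold crossings may be tabulated by the same strata as a supplement. Keep the pooled safety tables, and assert no direction of bias.

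**Cost.** Analysis-plan wording and extra table columns; the record that defines the strata is already collected. Intervals are wider within strata, and stratum sizes are unknown because glucose tests are mostly collected only when available. Detection of rare events within the starter stratum falls to about 0.47 to 0.80 at a 0.04% rate, if starters are an assumed 20% to 50% of 8,000. That is why the pooled safety tables must stay.
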